## Abstract

Angola reports one of the highest infant mortality rates in the world, and anemia represents one of its important causes. Recent studies, in under-five children from the Bengo province of Angola, described high prevalence’s, suggesting malaria, undernutrition and urogenital schistosomiasis as important contributors for the occurrence and spatial variations of anemia. Educational community-based interventions, either in Nutrition and Water, Sanitation, Hygiene and Malaria are recommended to correct anemia. Herein, we designed a cluster-randomized controlled trial to study the efficacy of two educational-plus-therapeutic interventions in the reduction of anemia: one in nutrition and the other in WASH/Malaria. Socioeconomic, nutritional, anthropometric, parasitological and biochemical data will be collected from all willing-to-participate children, aging under four and resident in the Health Research Center of Angola study area. Considering the multifactorial causes of this condition, determining the efficacy of both interventions might help documenting weaknesses and opportunities for planning integrated strategies to reduce anemia.

## 1. Background

Anemia, especially severe anemia, is associated with increased child mortality rates [1]. Moreover, limitations in physical and cognitive development, leading to an increase in academic failure and susceptibility to infectious diseases, are also of great concern [1,2,3,4]. Regional studies conducted in the Dande municipality (Bengo province) reported a 57% prevalence of anemia in under-5 children, indicative of a severe public health problem [5]. In this setting, in addition to the expected association with undernutrition (responsible for nearly 13% of anemia cases), clusters of high risk of anemia were found to overlap with *Plasmodium falciparum* and *Schistosoma haematobium* risk zones (associated with 16% and 10% of the cases, respectively) [5,6].

Around half of anemia cases are estimated to result from Iron Deficiency (ID) [7]. However, in malaria endemic countries, routine iron supplementation remains controversial and is only undertaken with caution, as the practice has been associated with both an increased incidence and severity of malaria, especially in non-iron-deficient anemic people [8,9,10,11,12]. Additionally, single nutrient deficiencies are rare, as insufficient ingestion of other hematopoietic micronutrients may occur and cause nutritional anemia. On the other hand, the high prevalence, intensity, reinfection and incidence rates of anemia-related infections can also contribute to iron deficiency anemia, potentially refractory to iron supplementation [2,5,13,14,15,16].

Integrating therapeutic (deworming) and preventive (either food-based or WASH/malaria education) strategies can simultaneously treat infections and increase hematopoietic micronutrient intake or reduce disease transmission, which could result in the reduction of malnutrition and anemia [2,14,17,18,19,20,21,22,23,24,25,26,27,28,29,30,31,32]. Several comprehensive intervention strategies have correspondingly been tested. However, they frequently evaluate the impact of education on nutrition or on infectious etiologies (whether or not combined with drug therapy) separately [17,18,19,20,21,22,23,24,25,26,27,28,29,31]. Thus, differences in their designs and methodologies hinder the comparison and evaluation of results, rendering it difficult to define the best approach to reduce anemia. For instance, differences on the target population (adult or children), dimensions of the learning package (e.g., for sanitation: stool disposal, water quality or supply), the delivers (community promoters/volunteers, teachers, local health workers, community leaders), the place where education occurs (at health center or at the communities), the number of intervention contacts, type of contacts (group meetings and/or individual contacts), duration of the intervention/observation and mainly the combination with other strategies (micronutrient supplementation, construction of latrines and hand-washing mechanisms, etc.) can be observed [17,18,19,20,21,22,23,24,25,26,27,28,29,31]. Furthermore, one of the most inclusive studies was published recently by Humphrey et al. 2019, and investigated the effect of two WASH interventions, either alone or combined with improved Infant and Young Child Feeding (IYCF), concluding that education in nutrition reduce anemia and stunting, but adding WASH to the intervention had no major improvements on those effects [33]. Similar results were reported by Null et al. 2018 within a cluster-randomized trial using interventive groups with several WASH and nutrition combinations [34]. Neither study investigated the effect of combining deworming, nor was the impact of malaria preventive actions included, and as far as we know, there are no published protocols or results of such studies implemented in Angola.

### 1.1. Aim

This paper describes the design of a cluster-randomized controlled trial that aims to compare the efficacy of two complex, community-based interventions: (1) nutritional education in the reduction of nutritional anemia, and (2) WASH/malaria education in the reduction of anemia caused by infection, both combined with a test-and-treat therapeutic approach.

### 1.2. Hypotheses under Study

(1) The nutrition arm assumes that the test-and-treat approach will clear infections and that education in nutrition will improve the knowledge and awareness of caretakers as regards the causes, prevention and treatment of nutritional anemia, which in turn may result in behavioral changes that reduce the prevalence of inadequate breastfeeding and IYCF. This could in turn improve dietary diversity, by increasing the consumption of erythropoietic-rich foods (iron, vitamin B12, vitamin A and folate) and enhancers of iron absorption (vitamin C), and decreasing the inadequate consumption of iron absorption inhibitors (polyphenols, phytates, calcium, etcetera)) [24,35,36], leading ultimately to a decrease in the prevalence of nutritional anemia.

(2) The WASH/malaria arm assumes both that the test-and-treat approach clears infections, and that education in appropriate water, sanitation, personal hygiene and malaria prevention practices improves the knowledge of caretakers regarding the causes and preventive measures against infections, which in turn would lead to behavioral changes, and consequently to reduced prevalence, intensity, incidence and re-infection rates of those diseases [31,37,38,39,40]. Thus, considering that parasitic infections are important causes of anemia within this setting, this intervention would consequently decrease the occurrence of infection-related anemia.

In our study, the intervention in the control group targets the treatment of infections, the intervention in the nutrition arm targets nutritional anemia and nutrition-related causes, and the WASH/malaria intervention focuses on infections and infectious-related anemia. Furthermore, it should be considered that non-malarial infections can also cause anemia through nutritional deficiencies, by causing blunted intestinal villi (which lead to impaired micronutrient absorption) [41]. Thus, by trying to prevent anemia through these 3 possible pathways, we can simultaneously investigate (1) whether combining education in nutrition with a test-and-treat approach could reduce nutritional anemia more than only treating intestinal/urogenital and malaria infections; (2) whether combining education in WASH/Malaria with a test-and-treat approach could reduce nutritional anemia more than only treating intestinal/urogenital and malaria infections; and 3) which of the educational interventions can prevent nutritional anemia the most.

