### 5.2. Baseline Assessment Eevaluations

The nutritional quality of children’s diets (24–36 months) will be determined in accordance with the Children’s Individual Dietary Diversity Score Indicator (IDDS) [69,70]. The prevalence of malnutrition in children will be calculated by WHO Anthro software (version 3.2.2). The chi-square test will be used to compare proportions, in addition to calculating the attributable fractions.

Pre-and post-intervention and intervention versus control arms evaluations.

Primary and secondary impact indicators will be evaluated between the baseline and the follow ups (for each study sample), and between the intervention and control arms. Outcomes will be compared analyzing for variance in the continuous variables and logistical regression for the categorical variables. Adequacy and plausibility arguments will be used, by analyzing the process indicators (described in Table 2) in accordance with the conceptual maps. Relative risk will be calculated in order to compare the cumulative incidence of anemia among the intervention and control arms.

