1. Primary outcomes 1.1 Impact on health - Variation of hemoglobin levels; - Anemia prevalence reduction. 2. Secondary outcomes 2.1 Impact on Health - Iron deficiency anaemia reduction; - Micronutrient deficiencies (iron, folate, vitamins A and B12, zinc and vitamin E serum levels); - Prevalence reduction, intensity, incidence and reinfections rates of STH, *P. falciparum* and *S. haematobium*; - Prevalence reduction of Stunting (height-for-age) and wasting (weight-for-height). 2.2 Impact on Behavior - Exclusive breastfeeding (0–5 months) and continued breastfeeding (12–15 months) [68]; - Increase of Minimum dietary diversity prevalence (6–23 months) [68]; - Increase of Minimum Meal Frequency prevalence [68]; - Increase of iron and vitamin A rich foods consumption; - Reduction of morbidity from diarrhea (reported).	1. Acquired knowledge - Theoretical test scores (evaluation of knowledge); - Practical test scores (evaluation of counseling performance); - Self-counseling efficacy evaluation. 2. Counseling performance - Number of families dropping outs from evaluation moments per technician; - Number of families successfully visited for counseling by each technician; - Number of notified participants present in each community groups per technician; - Number of scheduled visits held successfully per technician.	1. Acquired knowledge of receivers -Theoretical test scores; - Practical test scores (participation in community groups); - Self-evaluation at mother-to-child care. 2. Participatory level of receivers (adherence) - N° of attendances to evaluation moments; - N° of scheduled visits (both in person and by telephone call) held successfully; - N° of scheduled visits that had to be redials due to absence or unavailability; - Mood state of the receiver between visits; - N° of attendances to communitarian group. 3. Household environment evaluation (observation) - N° of household hand washing mechanisms; - N° of communitarian latrines around the house; - Cleaning conditions classification of household latrines (if existent); - Cleaning conditions classification of the backyard; - Presence of pets loose in the yard and stool. 4. Mother-to-children care practices - Children using bednets; - Children sidewalks; - Children with clean nails.	1. Services provided at evaluation moments - N° of hospital-based consultation held for parasite treatment; - N° of domiciliary-based consultation held for parasite treatment; - N° of hospital-based consultation held for sickle-cell follow up; - N° of children referred to the emergencies with severe anemia, severe malnutrition and non-malarial fever who reported to have been followed. 2.Participatory level of receivers (adherence) - Proportion of child-caretaker pair present in all evaluation moments; - Proportion of child-caretaker pair presenting in all counseling moments; - Proportion of caretakers participating in all community groups; - N° of notified child-mother pair failing the hospital-based consultations for parasite treatment or sickle-cell follow up; - N° of child-mother pair failing to picking up the sickle-cell drugs.

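### The three study questions are set on nutritional anemia, which is not a listed outcome and not the stated WASH/malaria target, and section 5.2 does not name the Nutrition versus WASH/malaria comparison

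*Protocol article*

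**What the plan says.** **Aim (section 1.1).** The trial "aims to compare the efficacy of two complex, community-based interventions". Nutrition education is paired with nutritional anemia. The second intervention is described as "WASH/malaria education in the reduction of anemia caused by infection".

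**Hypotheses (section 1.2).** Hypothesis 1 ends in less nutritional anemia. Hypothesis 2 concludes that "this intervention would consequently decrease the occurrence of infection-related anemia".

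**Questions (end of section 1.2).** Question 1 asks whether nutrition education plus test-and-treat lowers nutritional anemia more than treatment of infections alone. Question 2 asks "whether combining education in WASH/Malaria with a test-and-treat approach could reduce nutritional anemia" more than that same comparator. Question 3 asks "which of the educational interventions can prevent nutritional anemia the most".

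**Outcomes (Table 2).** The primary health outcomes are the change in hemoglobin and "Anemia prevalence reduction", neither restricted by cause. Iron deficiency anemia, micronutrient deficiencies and the infection measures are secondary.

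**Analysis (section 5.2).** Impact indicators are compared between baseline and follow-up and between intervention and control arms, by analysis of variance or logistic regression. A relative risk will "compare the cumulative incidence of anemia among the intervention and control arms".

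**Discussion (section 6).** The authors expect to describe and compare the effects of the two interventions on the occurrence of anemia.

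**The concern.** A trial question should point to an outcome that is collected and to a contrast that is analysed. Here the target of the WASH/malaria arm changes from infection-related anemia (aim, hypothesis 2) to nutritional anemia (questions 2 and 3) to anemia of any cause (primary outcomes). An analyst who follows section 1.2 and one who follows Table 2 would answer different questions. The trial is unblinded (section 3.3), so it is best to settle which anemia is meant before results are seen.

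The second gap concerns the contrast. The aim is to compare two education packages, but the listed comparisons set intervention against control. If only those are reported, readers are likely to rank the packages by comparing two separate results against control, which is not an estimate of the difference between them.

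**Working it through.** The article states no sample size, power or significance level, so there is no figure to reproduce. The check is mainly a reading of the passages side by side.

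**Step 1. Target of each contrast.**

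| Contrast | Aim and hypotheses (1.1, 1.2) | Numbered question (1.2) | Primary outcome (Table 2) | Named in 5.2 |
|---|---|---|---|---|
| Nutrition v control | Nutritional anemia | Nutritional anemia | Hemoglobin; anemia of any cause | Yes, as intervention v control |
| WASH/malaria v control | Infection-related anemia | Nutritional anemia | Hemoglobin; anemia of any cause | Yes, as intervention v control |
| Nutrition v WASH/malaria | The two are to be compared, each with its own target | Nutritional anemia | Hemoglobin; anemia of any cause | No |

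Three results follow:
- None of the three questions matches a primary outcome.
- For WASH/malaria v control, aim, question and primary outcome name three different targets.
- Infection-related anemia has no question and is not a listed outcome.

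**Step 2. Does the bridging rationale close the gap?** Just before the questions, section 1.2 argues that non-malarial infections can cause anemia through nutritional deficiency, by damaging the intestinal villi and so impairing absorption. This supports asking about nutritional anemia in the WASH/malaria arm as an additional question. It excludes malaria, whose prevention is part of that arm. It also gives no reason for leaving out the infection-related target that the same section states.

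**Step 3. What would naming the third contrast take?** Assume, for illustration, equal arms, each with variance *v* for its estimated mean.
- Var(Nutrition − control) = *v* + *v* = 2*v*.
- Var(WASH − control) = 2*v*.
- Var(Nutrition − WASH) = 2*v*.

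The head-to-head contrast then has the same standard error as either comparison with control and needs no further data.

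**Step 4. Why two separate tests do not replace it (illustration only).** The two comparisons with control share the control arm, so under the same assumptions their correlation is *v* / 2*v* = 0.5. Suppose that both packages have the same true effect. Then P(exactly one significant) = 2 × (power − P(both significant)).
- Assumed 80% power, correlation 0.5: 2 × (0.800 − 0.687) = 0.226. If the two were independent: 2 × 0.8 × 0.2 = 0.32.
- Assumed 50% power, correlation 0.5: 2 × (0.500 − 0.333) = 0.333. If independent: 2 × 0.5 × 0.5 = 0.50.

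These powers are assumptions. The figures show a general fact about paired significance tests and do not predict this trial's results.

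**The case against.** **Condensed article.** The article may leave the list of pairwise contrasts to an analysis plan that is not shown. Analysis of variance, and a relative risk among the intervention and control arms, can be read as a three-arm analysis. This stands to the extent that the contrast is not named; one cannot say that it will never be estimated. But section 5.2 does list its comparisons, and the one that defines the aim is not among them. An overall test across three arms would also not estimate that difference. An analysis plan could not settle the anemia target without overriding one of the article's own passages.

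**Argued pathway.** Section 1.2 reasons towards nutritional anemia through impaired absorption, and section 1 adds that infections can contribute to iron deficiency anemia. This is fair, and question 2 is not baseless. It remains partial for the reasons in step 2.

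**Outcomes already all-cause.** Table 2 applies hemoglobin and all-cause anemia to every arm, and the relative risk in section 5.2 is not restricted by cause. This also stands. A reader might infer that the head-to-head verdict is built to favour nutrition, but that would follow only if the questions were answered on nutritional anemia and the outcome table were set aside. Nor does the article show that nutritional anemia is where WASH/malaria education has least effect.

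**Local shares of anemia.** A reader might also infer from section 1 that the questions discard about twice the share of anemia that they count: undernutrition is "responsible for nearly 13% of anemia cases", against 16% + 10% = 26% for *P. falciparum* and *S. haematobium*. The article does not support that ratio. Undernutrition is not the same as nutritional anemia; the same section says that around half of anemia cases are estimated to result from iron deficiency; and adding 16% and 10% assumes that the two do not overlap.

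**Conclusion.** The concern holds as an inconsistency between the aim, the questions, the outcomes and the named analysis. All three questions rest on an outcome that is not listed, the WASH/malaria question departs from the target given in the aim and in hypothesis 2, and one of the three contrasts needed is not named. This is more than missing detail: the article's own passages conflict, and the comparisons named in section 5.2 do not include the one on which the aim is built.

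The conclusion rests on the text alone. No direction or amount of bias is shown, and the plan nowhere says that the better package will be chosen by which one is significant against control. The percentages in step 4 therefore illustrate a risk under assumed power and do not measure the size of this problem. The wording in section 1.2 may be a drafting slip, which would make the correction easier but no less necessary before outcomes are analysed.

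**What to change.** 1. In section 1.2, set all three questions on the listed primary outcomes, hemoglobin and all-cause anemia. Bring section 1.1 and hypothesis 2 into line, so that nutritional and infection-related anemia describe the expected pathways.
2. In section 5.2, name three contrasts: Nutrition v control, WASH/malaria v control, and Nutrition v WASH/malaria.
3. Estimate the third directly, with a confidence interval, from the same analysis as the other two, allowing for clustering by hamlet.
4. Keep iron deficiency anemia and the infection measures as secondary pathway outcomes.

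**Cost.** Rewording of sections 1.1, 1.2 and 5.2, and one further contrast from data already collected. Arms, outcomes and visits do not change. The downside is multiplicity: 3 contrasts × 2 primary outcomes = 6 comparisons at each follow-up instead of 2 × 2 = 4. The plan should acknowledge this and say how it is handled.

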## 2. Materials and Methods

### 2.1. Study Setting

This study targets hamlets with functional primary health care facilities within CISA’s Dande HDSS study area [42]. The surveyed area is located in the Bengo Province (Dande municipality), and includes all the hamlets in the communes of Úcua, Caxito, Mabubas, as well as some hamlets in Kikabo and Barra do Dande [42]. Within this area, between 2010 and 2014, the total resident population varied between 63,081 and 58,645, with the percentage of under-5 children ranging from 17.7% to 13.9%. Additionally, the fertility rate varied between 4.8 and 3.7 births per woman, with the crude birth rate ranging from 40.4 to 24.2 live births/year/1000 people and the under-5 mortality rate fluctuating between 92.1 and 60.1 per 1000 live births [42]. As the entire population of Kikabo and Barra do Dande are not fully surveyed by the Dande HDSS, they will not be included in this study. Although 15 hamlets with health facilities are located within this area, only those providing daily primary care practices will be included in this study [43].

### 2.2. Study Design

#### Baseline Assessment (Pre-Intervention Evaluation)

There were two qualitative pilot studies: (1) to characterize mother-to-child nutritional practices (as a basis to structure the questionnaire) and (2) to design a locally adequate Food Photography Atlas (FPA) for children U5 (for the 24 h recall evaluation). The first study was conducted between August and September of 2014 and enrolled 808 children aging 0–59 months and their caretakers in a two-stage cluster sampling strategy. Using a Portuguese translated questionnaire, adapted from ProPAN 14, we collected data on children’s breastfeeding, feeding practices and detailed food consumption in the previous 24 h [44]. As a result, data regarding the commonly consumed food was collected and a preliminary FPA S was produced. Following this, the second study, aiming at validating the previously mentioned FPA and to allow for the collection of age and context-specific food portion and nutrient ingestion among preschool children from the Bengo province, was conducted between February and March 2015. This was a convenient cross-sectional study that enrolled 75 primary caretaker residents in the Mabungo and Riceno hamlets within CISA’s study area. In sum, dishes were prepared according to local recipes, food photographs were produced, tested and selected, portion sizes were estimated and validated, and the reproducibility of this tool was evaluated. These results are being published elsewhere.

Using these tools, a pre-intervention evaluation, aiming to characterize the study population regarding anemia and its etiologic profile (by specific age groups (children aged under 6 months, between 6 and 23 months and between 24 and 36 months), will be performed.

